## Abstract

**Background:**

Informal caregivers (IC) of people with dementia (PwD) are at greater risk of developing physical and mental health problems when compared to the general population and to IC of people with other chronic diseases. Internet-based interventions have been explored for their potential to minimize the negative effects of caring, accounting for their ubiquitous nature, convenient delivery, potential scalability and presumed (cost) effectiveness. iSupport is a self-help online program developed by the World Health Organization (WHO) to provide education, skills training and support to IC of PwD. This paper describes the design of an intervention study aimed at determining the effectiveness of a Portuguese culturally adapted version of iSupport on mental health and other well-being outcomes.

**Methods:**

The study follows an experimental parallel between-group design with two arms: access to the five modules and twenty-three lessons of “iSupport” for three months (intervention group); or access to an education-only e-book (comparison group). One hundred and eighty four participants will be recruited by referral from national associations. Inclusion criteria are: being 18 years or older and provide e-consent; being a self-reported non-paid caregiver for at least six months; of a person with a formal diagnosis of dementia; being skilled to use internet; and experience a clinically relevant level of burden (≥ 21 on Zarit Burden Interview) or depression or anxiety symptoms (≥ 8 on Hospital Anxiety and Depression Scale). Data is collected online, resorting to self-administered instruments, at baseline, 3 and 6 months after baseline. The primary outcome is caregiver burden, measured by the Zarit Burden Interview. Symptoms of depression and anxiety, quality of life, positive aspects of caregiving and general self-efficacy are secondary study outcomes. The data analysis will follow an Intention-to-treat (ITT) protocol.

**Discussion:**

This protocol is an important resource for the many organizations in several countries aiming to replicate iSupport. Findings from this intervention study will offer evidence to bolster an informed decision making on scaling up iSupport as a new intervention program with minimal costs aimed at minimizing the psychological distress of IC of PwD in Portugal and elsewhere.

**Trial registration:**

ClinicalTrials.gov, NCT04104568. Registered 26 September 2019.

## Background

Worldwide, there are 9.9 million new cases of dementia each year, 2.5 million of those identified in Europe [1]. In 2015, it was estimated that 47.5 million people lived with dementia across the globe [2]. Dementia is a syndrome caused by neurodegenerative diseases affecting memory, thinking, behaviour and the ability to perform daily activities. Among older adults, this group of diseases is one of the main causes of disability and dependence, thus people with dementia (PwD) often require long term or permanent care [3].

Caring responsibilities are mostly assumed by family members and other informal caregivers, especially in lower-middle income countries and in countries characterized by a familialistic tradition [4–6]. Informal caregivers (IC) provide unpaid and ongoing assistance with basic or instrumental activities of daily living to a person with a disability or chronic illness [7]. While those caregivers may experience positive intrinsic reinforcement from the experience of caring, they are also often exposed to several stressors including financial problems, time constraints and care management issues [8]. As a consequence, when compared with both the general population and IC of people with other chronic diseases, IC of PwD are at a greater risk of developing depression and anxiety disorders, as well as hypertension, digestive, and breathing problems [8–11]. Caregivers’ psychosocial variables - including the experience of stress, burden and mental disorders, and the perceived inability to provide care - were previously related with abusive or harmful behaviours towards the care recipients [12], and identified as predictors of the care receiver’s institutionalization [13–15]. Reducing the negative effects of caring is instrumental to prevent undesired upshots for both the IC and the care receivers.

As higher levels of stress tend to be experienced by a person if coping resources are perceived to be less than one demands, IC tend to benefit from looking for external resources that might support them in dealing with stress, as well as in providing PwD with quality care [16, 17]. Interventions targeting IC vary in their style of administration and content, including psychoeducational interventions, supportive interventions, respite care, psychotherapy, interventions to improve care receivers’ competence/skills, and multicomponent interventions [18]. Regarding the efficacy or effectiveness of those interventions, some outcomes may be more responsive to certain types of interventions than to others and effect sizes may be influenced by the intervention type (specific effects) [18]. Current evidence suggests more robust effects for psychoeducational and multicomponent interventions (including, e.g. skills training, psychoeducation, techniques for self-care, changes in the caregiver’s setting) on subjective well-being, caregiver burden, depression and anxiety symptoms, skills/knowledge and self-efficacy [10, 18–21].

In spite of demonstrated beneficial effects of such interventions on numerous caregiver outcomes, several reports have been stressing the existence of situational barriers impeding IC of PwD of accessing it when delivered in its usual face-to-face format [8, 22–25]. Barriers may hamper the offer of those intervention programs (e.g. geographical inequalities, lack of trained workforce, infrastructures to scale up services, and/or funds); or may prevent IC from participating (e.g. social stigma, not managing to make a break from caregiving responsibilities or to arrange transport) [8].

To overcome such barriers, online training and support programs have been increasingly explored, accounting for their ubiquitous nature, convenient and privacy-preserving delivery, as well as potential scalability and presumed (cost)effectiveness [25–27]. The number of scientific publications on the use, acceptability and effectiveness of Information and Communication Technologies (ICT)-based interventions for IC of PwD (including but not limited to internet-based interventions) increased by 13% each year from 1990 to 2016 [28]. Several recent systematic reviews and meta-analysis examined the evidence on the effectiveness of internet-based intervention programs delivered to IC of PwD on a plethora of outcomes [29–33]. Beneficial effects were mostly reported on the reduction of anxiety and depression symptoms [29–33], perceived stress and burden [31–33] (not found in [29]), as well as on the increase of self-efficacy [31, 32], even if effects can be small [31]. Multicomponent interventions, tailored to individual needs, offering contact with other caregivers and coaching were reported as most beneficial [31, 33]. Reviews not defining specific outcomes as inclusion criteria for intervention studies show that most frequently studied outcomes include depression and anxiety symptoms and overall mental health, stress and burden, self-efficacy, knowledge, use of health services, positive aspects of caregiving and quality of life [31, 33]. Instruments used to measure such outcomes vary widely. In spite of some evidence in favor of internet-based interventions, inconsistent interventions (e.g. varied structure, duration, outcomes) and a substantial methodological diversity across studies tend to compromise a pooling of results [30, 31]. Moreover, the methodological quality of studies vary greatly and the lack of research details and quality reports seem to be important problems in the available literature [29]. In some cases, the overall evidence was considered low quality, hampering the interpretation and generalizability of the findings on effectiveness [31, 33]. Selection, performance, and reporting biases were present and a reason for concern [30, 31, 33], hence more well-thought research is welcome in this field.

## Methods

### Type of study, aims and research question

The study follows an experimental parallel between-group design with two arms aiming to determine the effectiveness of an online training and support program (iSupport, European-Portuguese version), as compared to a minimal education-only intervention (e-book on dementia and caregiving issues), to decrease caregivers’ burden, symptoms of depression and anxiety, and to increase quality of life, positive aspects of caregiving and self-efficacy, in IC of PwD. The intervention study is set in Portugal and planned to last six months. The research question - Can the Portuguese version of iSupport reduce perceived burden (primary outcome) and improve mental health, quality of life, and coping skills (secondary outcomes), in informal caregivers of people with dementia? - is addressed by the intervention study discussed in this paper. The Additional file 1 provides the SPIRIT checklist for recommended items to address in a protocol, applied to this intervention study.

### Selection of participants

#### Target population, inclusion and exclusion criteria

Informal caregivers of people with dementia are screened to assess whether they are (i) Portuguese adults (≥18 years); (ii) giving consent to participate (Electronic Informed Consent); (iii) providing non-paid care for at least 6 months at the time of the recruitment; (iv) caring for a person holding a formal diagnosis of dementia; and (v) be skilled to use the internet. For inclusion, the IC (vi) must also experience either a clinically relevant level of subjective burden, determined by a total score ≥ 21 on the Zarit Burden Interview (ZBI) [48, 49] or depression or anxiety symptoms, determined by a score ≥ 8 in at least one of the subscales of the Hospital Anxiety and Depression Scale (HADS) [50, 51]. Participants matching the inclusion criteria will be excluded if (i) they are unable to comprehend written Portuguese or (ii) do not have access to a device with internet connection at least twice a week. If (iii) the care receiver is in institutional care (e.g. nursing home or continued care unit), the participant is also excluded. How each inclusion and exclusion criteria are ascertained is described below (see 2.2.2. Sampling and recruitment). Both excluded participants and participants assigned to the control group will be offered the opportunity to use iSupport after the study closure, in case of manifested interest.

#### Sampling and recruitment

A consecutive (nonprobability) sampling strategy is employed, by consecutively selecting subjects who meet the entry criteria. Potential participants are referred by health professionals from national Alzheimer’s associations (not for profit organizations offering support in the community to IC of PwD) who are aware of the formal dementia diagnosis of the care receivers. Due to feasibility constraints, an independent diagnosis or second diagnosis of the care receivers will not be obtained. The process of recruiting and selecting the participants is illustrated in Fig. 1. First, health professionals identify the IC of PwD and verify the compliance with inclusion criteria i., iii., iv. and v. (see section Target population, inclusion and exclusion criteria). IC complying with these criteria and not matching the exclusion criteria are provided with the participant information sheet and invited to express their interest in enrolling in the study. IC that have expressed their interest are provided with a link to the online study platform and a user code/password (1) to access the platform. In case the participants declining to participate express their motives for taking that decision, those motives are noted with their consent, as a mean to control for barriers to participation and selection bias. Upon accessing the study online platform for the first time (at the time and place of their convenience), participants must provide an email contact and authorize its use to receive information about the study and will be prompted to complete a questionnaire aimed at determining or double-checking the compliance with inclusion criteria i., ii., iii., v., and vi. (see section Target population, inclusion and exclusion criteria). While the referral process aims to minimize the chances of volunteer bias, matching a specific referred person with a user accessing the platform would require complex arrangements, thus inclusion criteria verified at the referral process are double-checked with the online questionnaire. Due to feasibility constraints, a clinical evaluation of burden, anxiety and depression symptoms (inclusion criteria vi.) will not be conducted, instead these symptoms will be assessed by well-established self-report instruments (see sectionVariables and data collection methods) delivered via the study online platform. If the potential participants have a score indicating severe symptoms of anxiety and/or depression, a message is displayed in the screen recommending the participant to consult local mental health services.

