### Randomization and blinding

Eligible participants are randomly assigned to the intervention or to the control arm by using a permuted block randomization strategy to maintain reasonably good balance among groups. Blocks of four with equal number of As (intervention) and Bs (control) will be used, with the order of interventions within the block being randomly permuted (1 = AABB, 2 = ABAB, 3 = ABBA, 4 = BAAB, 5 = BABA, 6 = BBAA). Baseline characteristics of individuals randomized to each condition will be compared to verify if the randomization was successful. Health professionals referring the participants to the study platform are not aware of the randomization sequence, and even if they were, they could not control the participants’ allocation as they could not predict the sequence status at the time of the participants’ access to the study platform. Similarly, the researcher assigning the participants to each arm has no control over the order of enrolment (i.e. over who will access the online platform and when), and differs from the researcher performing the statistical analysis at a subsequent stage. The data analyst will be blinded to the intervention assigned to the participants. The study is single-blinded: participants are not unaware of the intervention received as they are active parts of the intervention. Data collection at baseline and outcome assessments are carried out in a computerized manner via study platform and resorting to self-administered instruments, thus the researcher has no influence over the measurements.

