#### Covariates

Variables measured at baseline (*t*_0_) include sociodemographic characteristics of IC, namely their age, gender, marital and occupational status, years spent in education and residence area. In addition, a questionnaire for caregiving characterization collects information on the type of care provided, i.e. paid/non-paid (screening); duration (number of years providing care) and frequency of care provision (number of hours per week); existence/non-existence of other care providers; relationship with the care receiver; and cohabitation/non-cohabitation with the care receiver. Moreover, age and gender of the care receiver are collected, as well as information on the care receiver’s living arrangements (living in the community vs. institutional care; screening), on the degree of care receiver’s dependence (as subjectively evaluated by the IC); and on the duration of dementia symptoms (as perceived by the IC). ICT usage is characterized by the frequency of internet use.

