### Sample size calculation

As a baseline for estimating the sample size, the primary null hypothesis was stated:*H0: The change in mean caregiver burden from baseline at t*_1_
*is the same in informal caregivers of people with dementia assigned to the iSupport program as in those assigned to a minimal education-only intervention.*

A two-sided alternative hypothesis was assumed:*H1: The change in mean caregiver burden from baseline at t*_1_
*is different in informal caregivers of people with dementia assigned to the iSupport program as in those assigned to a minimal education-only intervention.*

Caregiver burden at *t*_1_ (measured with the ZBI) is the primary outcome measure, therefore used for the sample size calculation. The effect size was defined taking into account a meta-analysis reporting a mean standardized effect size of 0.65 (95% confidence interval [0.46–0.84]), for multicomponent interventions, on caregiver burden [18]. Assuming a smaller but still moderate standardized effect size of 0.5 (E/S), equivalent to about a 6-point endpoint mean difference, and a SD of 12 based on Bachner and Rourke [63] and assuming an *α* (two-sided) = 0.05 and a β = 0.2, a sample size of 64 per group was calculated as follows:

*Standardized effect size (E/S) = 6 ÷ 12 = 0.5.*

16 ÷ (standardized effect size)^2^ = 16 ÷ 0.25 = 64

Conservatively allowing for a larger dropout rate of 30% found in the literature for these interventions [47], a total of 92 informal caregivers per group was calculated:

16 ÷ 0.25 × 1.43 = 92

With a sample size of 92 per group and a dropout rate no larger than 30%, the study will be able to detect an intervention effect of 0.5 for the primary outcome.

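### Enrolment is not limited to one caregiver per person with dementia, so co-carers may be split between arms, with a risk of contamination

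*Protocol article*

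**What the plan says.** The section on target population, inclusion and exclusion criteria lists six inclusion and three exclusion criteria. Those tied to the care receiver are a formal dementia diagnosis and not living in institutional care. The list does not mention a second caregiver of the same person and does not require the main caregiver.

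Sampling and recruitment takes eligible caregivers consecutively. Referring professionals make the first check: "First, health professionals identify the IC of PwD and verify the compliance with inclusion criteria i., iii., iv. and v". An online questionnaire then repeats most of these checks and adds consent and symptom level. The same section notes that linking a referred person to a platform user would be complicated to arrange.

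Allocation is by individual caregiver, in order of entry into the database. Randomization and blinding states: "Blocks of four with equal number of As (intervention) and Bs (control) will be used". It does not refer to the care receiver.

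Covariates shows that shared care is foreseen. The baseline questionnaire records "existence/non-existence of other care providers; relationship with the care receiver; and cohabitation/non-cohabitation with the care receiver". These items describe the sample; the article does not use them to restrict entry or to link participants.

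**The concern.** Two unpaid caregivers of one person, for example a spouse and an adult child, can each meet every listed criterion, enter separately and be allocated separately. If they land in different arms, the control participant shares a care receiver with an iSupport user.

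According to the article's description of the intervention, iSupport teaches problem-solving, cognitive reframing and analysis of what triggers behaviour. These skills can be talked over at home, and participants are not blinded. They can also change how the care receiver is looked after, and so the burden felt by a co-carer who never logs in. Either route would most likely lower burden in the control arm and dilute the primary comparison of ZBI change at three months.

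The sample size has no margin for dilution. The only allowance above 64 per group is for 30% dropout.

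**Working it through.** **Inputs from Sample size calculation.** Two-sided alpha 0.05, beta 0.2; "Assuming a smaller but still moderate standardized effect size of 0.5 (E/S), equivalent to about a 6-point endpoint mean difference"; SD 12; 30% dropout; "a total of 92 informal caregivers per group was calculated".

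**Inputs that the article does not give (assumptions).** *f* is the share of participants who have an enrolled co-carer, taken as 5% to 30%. *s* is the share of the effect passed to a control co-carer, taken as 50% to 100%.

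**1. The plan's own figures.** 16 / 0.5² = 64 per group. 64 / 0.7 = 91.4, so 92 (the article's 64 × 1.43 = 91.5 also rounds up to 92). Power at 64 per group by the normal approximation: the standard error is 12 × √(2/64) = 2.121, 6 / 2.121 = 2.828, and Φ(2.828 − 1.960) = 80.7% (80.1% by the t-test). The stated figures reproduce.

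**2. Probability *d* that a pair is split.** Enumerating the six listed blocks, two people in the same block of four are in opposite arms with probability 2/3. In different blocks it is 1/2. For two consecutive entrants it is 3/4 × 2/3 + 1/4 × 1/2 = 0.625.

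**3. Dilution.** Let c = f × d × s. The expected difference becomes 6 × (1 − c), and power is Φ(6(1 − c) / 2.121 − 1.960). Enrolment per arm that restores the planned power is 64 / (1 − c)², rounded up, then divided by 0.7 and rounded up.

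Example with f = 10%, d = 2/3, s = 1: c = 0.067, difference 5.60, 5.60 / 2.121 = 2.640, power Φ(0.680) = 75.2%. Enrolment: 64 / 0.871 = 73.5, so 74; 74 / 0.7 = 105.7, so 106.

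The first value in each cell is for d = 1/2, s = 50%; the second is for d = 2/3, s = 100%.

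| f | c | Difference (points) | Power at 64 per group | Enrolment per arm to restore power |
|---|---|---|---|---|
| 0 | 0 | 6.00 | 80.7% | 92 |
| 5% | 0.013 to 0.033 | 5.93 to 5.80 | 79.8% to 78.1% | 95 to 99 |
| 10% | 0.025 to 0.067 | 5.85 to 5.60 | 78.7% to 75.2% | 98 to 106 |
| 20% | 0.050 to 0.133 | 5.70 to 5.20 | 76.6% to 68.8% | 102 to 123 |
| 30% | 0.075 to 0.200 | 5.55 to 4.80 | 74.4% to 61.9% | 108 to 143 |

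**4. Correlation within pairs.** With intraclass correlation ρ (assumed 0.3 to 0.5), the variance of the arm difference is multiplied by 1 + f × ρ × (1 − 2d). For f of 10% to 30% and d of 1/2 to 2/3 this lies between 0.95 and 1.00 (for example 1 + 0.3 × 0.5 × (1 − 4/3) = 0.95). It does not exceed 1 in this range, so treating participants as independent does not understate the variance.

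**The case against.** The strongest reply is that this is a possibility and not an observed fact. The article does not say that co-carers will be invited, how many there might be, or that content is shared. iSupport sits behind an individual user code and password. Each co-carer must separately be able to use the internet and reach a burden or symptom threshold, which will exclude some pairs. The article is also a condensed account: the selection flowchart and any referral instructions are not shown, and a one-caregiver practice could exist there. All of this stands as to frequency. It does not close the gap, because the entry criteria are set out as a list and would admit both caregivers.

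Four stronger readings are tempting and are not supported:

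- **That contamination of controls will occur.** A pair is split with probability 1/2 to 2/3, and transfer is assumed. For 10% of controls to receive the full effect, about 0.10 / 0.625 = 16% of participants would need an enrolled co-carer with complete transfer, or 32% with half transfer.
- **That blocking causes the split.** Participants log on when it suits them. Pairs in different blocks split with probability 1/2, as under simple randomisation.
- **That correlated scores invalidate the test.** The variance factor of 0.95 to 1.00 rules this out as a practical problem.
- **That pairs could never be traced.** No care-receiver identifier is mentioned, but its absence is an inference. The care receiver's age and gender and the caregiver's relationship and cohabitation are collected, so likely pairs might be flagged.

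The direction of bias is also not certain. If the iSupport user handed tasks to the control co-carer, control burden could rise and the difference widen.

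**Conclusion.** The point holds as a gap in the stated design. As written, co-carers of one person may both enrol and be randomised to opposite arms. This carries a risk of contamination that would most likely dilute the ZBI difference.

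The size depends on two quantities that the article does not give. On the assumed ranges, power falls by about 1 to 3 percentage points at 5% co-enrolment and 2 to 6 at 10%, which is modest. At 20% the loss is 4 to 12 points, which is material. The point is worth acting on because prevention is cheap and analysis after the fact could correct the problem only imperfectly.

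**What to change.** - Add an entry criterion: only one caregiver per person with dementia may be enrolled.
- Have the referring professional, who already knows the care receiver and is the point of referral, issue one platform code per care receiver. This does not require matching referred people to platform users.
- Add one screening item asking whether another carer of the same person is already taking part, and end the questionnaire if the answer is yes. The questionnaire already stops for ineligible people. This item covers families referred by more than one route.

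With this rule f is zero, provided codes and answers are reliable, and the stated 92 per arm stands. The restriction acts before allocation, so it does not disturb the randomised comparison.

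The cost is one line of eligibility text, one screening item and the loss of a few second caregivers in a trial that expects recruitment to be hard. They can be offered iSupport after the study closes, as the article already provides for excluded participants. If they must be kept, a heavier alternative is to randomise co-carers together and account for the pairing in the analysis.
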